### Estimation of sample size

The primary outcome in this study is the proportion of subjects with chemotherapy-induced dermatologic toxicity as measured by National Cancer Institute Common Terminology Criteria for Adverse Events (NCI CTCAE) specific grade ≥2. According to previous research, the incidence of NCI CTCAE specific grade ≥2 after the intervention is about 30 % [12]. Our pilot study showed that about 10 % of subjects would have NCI CTCAE specific grade ≥2 after taking the YH0618 soup; thus, the difference in proportion of subjects with dermatologic toxicity between the soup group and waiting-list control group is 20 %. The difference in proportion between the two groups will be examined by a Z-test. To achieve a type I error alpha = 0.05 and power (1 – beta) = 90 %, the minimal number of subjects needed in each group is 82. We estimated a 30 % attrition rate at the end of follow-up; hence, a sample size of at least 118 in each group (236 in total) is planned for this study.

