### Intervention and control conditions

Prior to intervention, baseline data will be collected including demographics, chemotherapy-induced dermatologic toxicity, skin color, nail color, tongue color, score of fatigue, and the indexes of myelosuppression, hepatotoxicity, and nephrotoxicity in the blood. After that, participants assigned to group A will receive YH0618 soup 6 days/week for 6 weeks and uncontrolled follow-up for 6 weeks, while group B are required to wait for 6 weeks and then receive YH0618 soup for 6 weeks. There is no contraindication between YH0618 soup and chemotherapy, because all the components are general food which people often eat in their daily lives.

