*Nephrotoxicity:* Liver and kidney function are important indicators in evaluating drug safety. Moreover, based on the theory of homogeny of liver and kidney in Chinese medicine, it is necessary to test kidney function. In the testing of kidney function, injury to the kidney can be exactly reflected by creatinine in the blood. The concentration change of creatinine is determined by the glomerular filtration rate, and only at a rate down to one-third of normal will the creatinine increase significantly [35]. In addition, blood urea nitrogen (BUN) is an important indication of renal (kidney) health. Therefore, creatinine (Cr) and BUN will be used as indexes to assess nephrotoxicity.

All participants will be assessed before the intervention (baseline), and 3, 6, and 12 weeks after intervention. All YH0618 materials conform to Food and Environmental Hygiene Department’s requirement for food safety and achieve the certificate of quality. The packing will be conducted at clinics of the School of Chinese Medicine, HKU. A professional research assistant will teach the subjects how to decoct the YH0618 soup, and the specific intake, water amount, and decoction time will be provided to each subject. These subjects will be asked to complete the questionnaires, undergo blood tests by themselves in hospitals, and send all testing results. Quality and compliance to intervention will be achieved by checking attendance records and the diary of self-record kept by each participant. All outcome assessors will be blinded to the intervention types of participants.

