### Statistical analysis

Statistical analysis will be conducted by a statistician using SPSS version 22.0. Analyses will be performed based on intention-to-treat principles, and any missing data in the follow up visits will be imputed using multiple imputation.

Descriptive statistics will be used to summarize the baseline demographics and clinical characteristics for both groups. Missing values at follow-up visits or drop-outs in the two groups will be assessed to identify any potential bias.

For the primary outcomes, relative risk for the incidence of dermatologic toxicities with grade ≥2, including 95 % CIs obtained via normal approximation to the binomial distribution, will be analyzed for the two groups. The changes in nail color and skin color from baseline to 6 weeks will be compared between the two groups by independent sample *t* tests. Because participants will be randomized into the intervention group or wait-list group, little confounding is expected. However, potential confounding variables will be identified as those that differ among treatment groups at baseline and are significantly associated with outcomes. In case any potential confounders are identified, a logistic regression model and a multiple linear regression model will be used to analyze the binary and continuous outcomes, respectively.

In further analyses using measures at all time points, the relative effectiveness of the interventions, including all primary and secondary outcomes, will be assessed in repeated measures mixed models, using the generalized estimating equation (GEE) modeling method. The repeated measures regression models account for the correlations between individual measurements when repeated over time. The primary test of effect depends upon differing patterns of change (slope) over time; thus, differences in slope will be identified by significant interactions of intervention group with time. If the interaction terms are significant, then further analyses will use contrasts within the models to compare groups at each time point and to compare outcomes across time within each group.

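### The slope interaction called the primary test of effect spans week 12, after the wait-list arm has had the soup, so it does not measure soup versus no soup and it gates the week-6 contrast for several outcomes

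*Protocol article*

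**What the plan says.** The Statistical analysis section of the protocol article describes two layers of between-group analysis.

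- For the primary outcomes it gives a relative risk with 95% CI for grade ≥2 dermatologic toxicity, and independent-sample t tests of nail and skin colour change from baseline to week 6.
- It then adds a GEE model: "In further analyses using measures at all time points, the relative effectiveness of the interventions, including all primary and secondary outcomes" are to be assessed in it. Within that paragraph it states: "The primary test of effect depends upon differing patterns of change (slope) over time; thus, differences in slope will be identified by significant interactions" of group with time. Comparisons at single visits are conditional: "If the interaction terms are significant, then further analyses will use contrasts within the models to compare groups at each time point".

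Other sections fix the design around this model.

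- Visits (Clinical objective examination; Table 1 agrees): "All participants will be assessed before the intervention (baseline), and 3, 6, and 12 weeks after intervention".
- Treatment (Intervention and control conditions): group A takes the soup for 6 weeks and then has 6 weeks of uncontrolled follow-up, "while group B are required to wait for 6 weeks and then receive YH0618 soup for 6 weeks".
- The Abstract and the Primary outcome section place the primary outcome at 6 weeks.
- Estimation of sample size: "The difference in proportion between the two groups will be examined by a Z-test".

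**The concern.** Treated and untreated patients are compared only from baseline to week 6. Between weeks 6 and 12 the arms swap: group B starts the soup and group A stops. A slope fitted through week 12 mixes the effect of the soup, its persistence in group A and the delayed response in group B. The article nevertheless calls this slope difference the primary test of effect, although the trial is sized on a two-proportion Z-test and the preceding paragraph assigns other tests to the primary outcomes.

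Two things are at stake. First, two analyses carry the word primary, and nothing says which decides if they disagree. Second, tongue colour (a primary outcome that the t-test sentence does not name), fatigue and the blood, liver and renal measures have no other clearly planned between-group test. For them the week-6 contrast is examined only if the interaction is significant.

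**Working it through.** **The sample size matches the week-6 comparison.** Inputs from Estimation of sample size: 30% versus 10%, alpha 0.05 (two-sided assumed), power 90%, attrition 30%. With pooled proportion 0.20:

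n = [1.96·√(2·0.2·0.8) + 1.2816·√(0.3·0.7 + 0.1·0.9)]² / 0.2² = (1.1087 + 0.7019)² / 0.04 ≈ 81.96, so 82 per group; 82/0.7 = 117.1, so 118 per group. Both stated figures are reproduced. They belong to a single comparison of proportions, not to a slope.

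**Leverage of each visit on a linear slope.** Times 0, 3, 6, 12 have mean 5.25. The deviations are −5.25, −2.25, 0.75 and 6.75, and Sxx = 27.5625 + 5.0625 + 0.5625 + 45.5625 = 78.75. Week 12 supplies 45.5625/78.75 = 58% of Sxx; week 6 supplies 0.5625/78.75 = 0.7%.

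**Slope of the A-minus-B difference.** Assume the benefit d builds linearly to week 6. The difference is then 0, −0.5d and −d at weeks 0, 3 and 6, and x at week 12. The article gives no week-12 values, so x is varied.

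Slope difference = [(−2.25)(−0.5d) + (0.75)(−d) + 6.75x] / 78.75 = (0.375d + 6.75x) / 78.75

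| Assumption at week 12 | x | Slope difference per week |
|---|---|---|
| B gains nothing, A keeps its benefit | −d | −0.081d |
| B gains half, A keeps its benefit | −0.5d | −0.038d |
| B gains 75%, A keeps its benefit | −0.25d | −0.017d |
| B gains all, A keeps its benefit | 0 | +0.005d |
| B gains all, A loses half | +0.5d | +0.048d |

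Over weeks 0, 3 and 6 alone (mean 3, Sxx 18) the slope difference is 3·(−d)/18 = −0.167d. The sign changes at x = −0.375d/6.75 = −0.056d. With full catch-up, varying the onset from late to early moves the result only between −0.010d and +0.019d.

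**Simulation on the binary outcome.** Logistic GEE with robust standard errors, 82 per arm. Group A is at 30/20/10% and group B at 30/30/30% for weeks 0/3/6. Only 30% and 10% at week 6 come from the article; the other rates and the latent within-patient correlation (0.5 or 0.6) are assumptions. Ranges are across separate runs of 300 to 2,000 replicates.

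| Test and week-12 assumption | Significant for soup | Significant for wait-list |
|---|---|---|
| Linear time, weeks 0–6 only | 91% | 0% |
| Linear time, all visits, B stays at 30% | 88–91% | 0% |
| Linear time, all visits, B at 20% | 52–57% | 0% |
| Linear time, all visits, both at 10% | 7–10% | about 1% |
| Linear time, all visits, A back to 20%, B at 10% | 0% | 27% |

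With visit as a category and both arms at 10% at week 12, the joint 3-df interaction is significant in 77–79% of replicates. Requiring it first, the week-6 contrast favours the soup in 72%; without that condition it does so in 89–92%.

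**The case against.** The strongest reply is that valid week-6 analyses are already planned without conditions. The article gives the relative risk and the week-6 t tests for the primary outcomes first, and introduces the GEE only afterwards as further analyses. The word primary can then be read as naming the main term within that secondary model. This stands. A reader might infer that the sound week-6 comparison may never be examined; that is not so for the incidence of grade ≥2 toxicity or for nail and skin colour.

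A second reply is that linear time is not stated. The word slope points to it, but the plural interaction terms and the contrasts at each time point also fit visit as a category. On that reading the effect is neither hidden nor reversed, although the gate costs power. This also stands, with the limit that a significant joint test over four visits partly reflects group B's own treatment.

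A third reply is that a null or reversed slope requires near-full catch-up by week 12, and the article gives no week-12 figures. A reader might infer that an effective soup must show no slope difference or one favouring the wait-list. The documents do not support that: with half catch-up the linear test still favours the soup in about half of simulated trials. Even under full catch-up the direction depends on scale: the least-squares slope is marginally positive, while the simulated logit slope is slightly in the soup's favour (−0.03 per week).

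Last, week 12 is not worthless. It remains a randomised comparison of immediate with delayed soup, so removing it from every model is one acceptable remedy among others.

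**Conclusion.** The point holds as a mislabelled test with the wrong time window. An all-visit slope interaction does not estimate soup versus no soup, because group B is treated before the last visit. Under linear time it dilutes the contrast from −0.167d to −0.038d per week with half catch-up, and to about zero with full catch-up. It turns against the soup (+0.048d) if group A also loses half its benefit. These sizes rest on linear onset to week 6 and on assumed week-12 values; the simulated rates also rest on an assumed baseline rate and correlation.

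The harm from gating falls on tongue colour, fatigue and the laboratory outcomes. The only other model mentioned is a regression used if baseline confounders are found, and it is described within the primary-outcome paragraph. For the incidence outcome and for nail and skin colour, what remains is the conflict over which analysis is primary.

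**What to change.** In the Statistical analysis section:

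1. Delete the sentence that makes the slope the primary test of effect.
2. State that the week-6 between-group comparison is the primary test for each primary outcome, tongue colour included.
3. In the GEE, code visit as a category and report the week-6 group contrast for every outcome, whether or not the interaction is significant. The model may be limited to weeks 0–6 or keep all visits.
4. Report week 12 separately as immediate versus delayed soup, not as soup versus no soup.

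This is a change of wording to be made before the data are unblinded. It needs no extra patients, visits or measurements, and it keeps the planned sample size tied to the comparison for which it was calculated.

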## Discussion

This is the first strict randomized controlled trial to evaluate the effect of medical food on ameliorating chemotherapy-induced toxicity. The proposed study may provide direct and convincing evidence to support YH0618 as an adjuvant treatment for reducing chemotherapy-induced toxicity, which could be introduced into clinical settings. Since little attention has been given to exploring the role of medical food intervention in reducing chemotherapy-induced toxicity, this study will provide solid scientific evidence for international healthcare policy makers to support the integration of alternative intervention strategies in providing care to patients with cancer. When considering that more and more cancer patients are facing chemotherapy-induced side effects even after they have completed chemotherapy, our achievements will provide a safe and effective way for reducing chemotherapy-induced toxicity and improving their quality of life. The objective assessments for chemotherapy-induced toxicity, such as color index, are another important advantage in this study.

However, the main potential limitation of this protocol is that it is not double-blinded. A placebo would not be used in this study, because it is difficult to make a dietary placebo with the limited manpower and finances at this stage. It is also more fair to the wait-list group, as all of the subjects have opportunities to drink the YH0618 soup. If the results are positive, we will further compare the differences of the YH0618 soup and a placebo in order to avoid psychological effects in the future. Although the participants are not blinded, all of the evaluators and statisticians are blinded.

### Trial status

Recruitment started in July 2015, and the trial is expected to be completed in June 2017.

## Abbreviations

Alba, albumin; ALT, alanine aminotransferase; AST, aspartate transaminase; BUN, blood urea nitrogen; CIE, International Commission on Illumination; Cr, creatinine; DSMB, Data and Safety Monitoring Board; FACIT-F, Functional Assessment of Chronic Illness Therapy-Fatigue; GEE, generalized estimating equation; HGB, hemoglobin; HKU/HA HKW IRB, Institutional Review Board of the University of Hong Kong/Hospital Authority Hong Kong West Cluster; NCI CTCAE, National Cancer Institute Common Terminology Criteria for Adverse Events; PLT, platelet; WBC, white blood cell
